### Statistical analyses

#### Plan of analysis

Continuous outcomes will be summarised and presented graphically as geometric means and standard errors, assuming that a natural logarithmic transformation will be applied to the data to normalise their distributions [50]. The primary outcome, Troponin-I, and the secondary outcomes such as markers of kinase activity, oxidative stress and inflammation, are all measured multiple times in each patient (see Table 1). Therefore, Troponin-I and the other markers will be analysed by fitting multilevel mixed effect linear regression models, which consider the repeated measures in an appropriate and efficient manner. These models will fit both fixed effects (intervention, surgical stratum, centre, time and the interactions of intervention x time and intervention x centre) and a random effect. The fixed effects are analogous to standard regression coefficients and are estimated directly. The random effect is not directly estimated but is summarized according to its estimated variances and covariance. Baseline (pre-intervention) measures, where available, will be analysed jointly with the post-intervention measure(s). The interaction of group and surgical stratum will be tested and, if statistically significant at the 10% level, the treatment effect will be reported for each stratum separately; otherwise, an overall treatment effect will be given. Similarly, interactions of group and time and group and centre, will be explored (overall or within stratum depending on the significance of the group by stratum interaction) and, if statistically significant at the 10% level, the treatment effect will be reported for each time point separately.

Analyses will be adjusted for stratification factors, namely surgical procedure and centre. Findings will be reported as effect sizes with 95% confidence intervals. Analyses will be based on the intention-to-treat; cross-overs are expected to be rare. The frequencies of complications and conversions will be tabulated descriptively, by pathology. However, the trial is not powered to detect differences in adverse events and no statistical comparisons will be carried out.

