### Challenges in study procedures

It has been suggested that some drugs interact with remote ischaemic preconditioning. Propofol and Fluorane, two of the most commonly used drugs in anaesthetic practice, are two such drugs. Propofol may inhibit STAT-5 transcription [51], hence reducing the preconditioning effect, while Fluorane may enhance protection [52]. However, there is a lack of firm evidence to substantiate these potential effects on the ischaemic preconditioning pathway. Therefore, for consistency, we have opted for the strategy of the ERICCA trial, which does not specify an anaesthetic protocol and allows each centre to follow its own practice. The two centres recruiting to this study adhere to their own, well-documented centre-specific protocols, minimizing variability in the anaesthetic procedures used between patients at the same centre. Stratified randomization ensures that patients allocated to both the intervention and control group within a centre will undergo the same anaesthetic procedures. Moreover, we will be able (albeit with low statistical power) to describe the interaction between centre and intervention.

Despite being a two-centre study, this study will recruit CABG patients at only one centre (ICHT). This is because the cardioplegia protocol for this operation differs between the two centres (warm blood versus cold blood), and it is believed that this might influence selected outcomes. This is hindering the recruitment rate, together with the challenges in recruiting patients to the AVR group in both centres because AVR operations are less frequent.

The intervention is carried out primarily in the anaesthetic room. Blinding of the operating team and carrying out the intervention can be challenging at this stage of the study because it coincides with the pre-operative anaesthetic procedures. The time a patient spends in the anaesthetic room can vary, and on some occasions the intervention can be incomplete by the time the patient is ready for theatre. To prevent delay of surgery, the intervention is completed in theatre as the patient is being prepared for surgery before sternotomy.

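### The 10% rule ties the group × centre test to effects by time point and names no by-centre output, so a centre signal would trigger a split that does not address it

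*Protocol article*

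**What the plan says.** The protocol article's Plan of analysis fits a mixed model whose fixed effects include the "interactions of intervention x time and intervention x centre". It then gives two reporting rules.

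- **Group × stratum:** "if statistically significant at the 10% level, the treatment effect will be reported for each stratum separately"; otherwise one overall effect is given.
- **Group × time and group × centre, in one sentence:** "Similarly, interactions of group and time and group and centre, will be explored", overall or within stratum according to the stratum result, and "if statistically significant at the 10% level, the treatment effect will be reported for each time point separately".

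The Subgroup analyses section plans nothing beyond what is described there. Under Challenges in study procedures, anaesthetic practice is left to each centre: "The two centres recruiting to this study adhere to their own, well-documented centre-specific protocols". The same section says that "we will be able (albeit with low statistical power) to describe the interaction between centre and intervention", and that CABG patients are recruited at one centre only.

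**The concern.** The stratum rule matches the breakdown to the factor tested. The next sentence begins as a parallel but loses the match for centre: two tests with different null hypotheses share one condition and one output. The group × time test asks whether the RIPC effect changes over time. The group × centre test asks whether it is the same at both centres. Rejecting the second leads, as written, to effects split by time and pooled over centres.

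Two things are at stake. First, time-point reporting of troponin, the primary outcome, can be set off by a test that carries no information about time. Second, if the centre test is significant, the rule does not call for the estimates a reader would then need. The protocol has its own reason to care about centre, since it notes that common anaesthetic drugs have been suggested to weaken or strengthen preconditioning and that the centres follow their own anaesthetic protocols.

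**Working it through.** **Inputs from the protocol (Sample size; Blood samples; Plan of analysis).** 60 patients per stratum and 120 in total, allocated equally; pre-post correlation 0.3; post-post correlation 0.5; five post-operative samples; 90% power at 0.43 SD overall; trigger level 10%. Assumed: two-sided 5% alpha for the power statement, independent interaction tests, and the second centre's share of AVR patients, which the article does not give.

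**1. The plan's own figure.** The variance factor for the mean of five post measures adjusted for baseline is (1 + 4×0.5)/5 − 0.3² = 0.51. The SE of the overall effect is √(0.51×2/60) = 0.130. Power at 0.43 SD is Φ(0.43/0.130 − 1.960) ≈ 91%, against 90% stated, so it reproduces. Working back from the stated 90% gives nearly the same SE: 0.43/(1.960 + 1.282) = 0.1327. This second value is used in step 3.

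**2. No interaction of either kind.**
- If only group × time triggers the time split: 10%.
- As written, either test triggers it: 1 − 0.9×0.9 = 19%.
- A simulation of 20,000 trials (CABG at one centre, AVR split 30/30, five equally correlated post measures) gave 18.9%, so independence is a fair approximation here.

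**3. A centre difference of 0.5 SD in AVR, no variation over time.** With n1 + n2 = 60 AVR patients at the two centres, the interaction SE is √(0.1327²×120×(1/n1 + 1/n2)), where 0.1327²×120 = 2.113. Power of the two-sided 10% test is Φ(0.5/SE − 1.645) + Φ(−0.5/SE − 1.645). The chance that the time split is triggered is 1 − 0.9×(1 − power).

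| AVR patients at second centre | SE | Centre-test power | Time split triggered |
|---|---|---|---|
| 12 of 60 (20%) | 0.469 | 28% | 36% |
| 24 of 60 (40%) | 0.383 | 37% | 43% |
| 30 of 60 (50%) | 0.375 | 38% | 44% |
| 36 of 60 (60%) | 0.383 | 37% | 43% |

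With time as the only trigger, the last column would be 10% in every row.

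**4. Other sizes of centre difference.** Using the 0.51 variance factor and a 30/30 AVR split (SE 0.369), the time split is triggered about 39%, 50% and 73% of the time for differences of 0.43, 0.55 and 0.80 SD. With a 15/45 split (SE 0.426) the figures are 34%, 43% and 63%.

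**5. Why AVR only.** One centre supplies all CABG patients and some AVR; the other supplies AVR only. A test over all 120 patients without a group × stratum term compares a mixed group with a pure AVR group. The same formula applied to all patients gives centre-test power of 31–53% and trigger rates of 38–58% when the second centre has 10–30% of the total. That test does not separate centre from pathology, so these figures are not used for the conclusion.

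**6. Precision of time-point effects.** With one post measure the variance factor is 1 − 0.3² = 0.91. The SE is larger than for the five-measure average by √(0.91/0.51) = 1.34, about a third.

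**The case against.** The strongest reply is that this is a drafting slip. The sentence follows on from the stratum rule, and the natural intention is that effects be given for each time point or each centre, respectively. That is plausible, and an analysis plan not shown here may say so. It does not remove the point: the protocol states a threshold and a consequence, and the consequence is wrong for one of the two tests. The Subgroup analyses section limits subgroup work to what is described, and by-centre effects are not described.

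A reader might infer that a real centre difference would be hidden. The document does not support that. The intervention × centre term is a fitted fixed effect, findings are to be reported with 95% confidence intervals, and the Discussion intends to describe the interaction. A reader might also infer that the overall effect is dropped when the rule fires. The sentence does not say so; only the stratum rule has a clause on when the overall effect is given.

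Nor does the protocol rest its handling of anaesthetic differences on this test. It relies on centre-specific protocols and stratified randomisation, adds the interaction as a low-power extra, and says that firm evidence for the drug effects is lacking. Finally, time-point effects remain valid estimates; they are less precise and answer a different question. All of this limits the consequence but leaves the mismatch in the rule standing.

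**Conclusion.** The point holds as a mis-specified reporting rule. Both interaction tests lead to effects by time point, and no by-centre output is named. That mismatch is a matter of text and depends on no assumption.

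Its size does depend on assumptions. The time split is triggered about 19% of the time instead of 10% when nothing varies, if the tests are independent. It is triggered about 36–44% of the time with a 0.5 SD centre difference in AVR, no time variation, and an assumed 20–60% of AVR patients at the second centre. The 0.5 SD is illustrative. The document does not support the stronger conclusion that a centre difference goes unreported.

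**What to change.** Separate the two tests in the Plan of analysis. Let only the group × time test lead to effects by time point. For group × centre, report the interaction estimate with its 95% CI and the treatment effect at each centre, beside the overall effect.

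State that the centre contrast is estimated within the AVR stratum, or from a model that also contains a group × stratum term. CABG comes from one centre, and the protocol itself expects a larger effect in AVR, so a pooled by-centre table would mix pathology with centre.

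The cost is about one sentence in the plan and one extra table row, with no new data. The downside is imprecise centre estimates, with an SE of roughly 0.37 to 0.47 SD for the interaction in the cases above. The protocol already concedes the low power, and the confidence interval would show it.

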Similarly, little is known about the changes in the target tissue (myocardium) that are brought about by RIPC *before* ischemia and reperfusion. Most studies that have investigated changes in the myocardium have done so *after* reperfusion. It has been suggested that a signalling factor triggers intracellular signal transduction mechanisms in the heart, which are similar to those involved in cardiac ischaemic pre- and post-conditioning [1]. These could include activation of pro-survival kinases of the reperfusion injury salvage kinase (RISK) pathway, which could protect the heart by inhibition of the mitochondrial permeability transition pore (MPTP) [1]. It is possible that a variety of other signalling pathways involved in MPTP regulation [31] could also be involved in RIPC-induced protection. A recent experimental study [32] investigated the differential role of mitogen-activated protein kinase pathways, which suggested that the phosphorylation of p38MAPK, Erk1/2 and JNK could be involved in RIPC. Experimental evidence supports involvement of the mitochondrial Ca^2+^-activated K^+^ channel [33]. A very recent observational clinical study reported that RIPC was associated with changes in the phosphorylation of the signal transducer and activator of transcription 5 (STAT5) [11]. Most of these studies point to the mitochondria as a potential target for inducing protection by RIPC. We hypothesise that kinases involved in regulating the permeability of the MPTP are the mediators of RIPC-induced cardioprotection. Therefore, these enzymes and related signalling pathways will be monitored to identify the main pathway(s) responsible.

A key difference that is likely to exist between RIPC and cardiac pre- and post-conditioning stimuli (where the heart is made ischaemic for short periods) is related to changes in energy rich phosphates. Thus, RIPC is not expected to trigger cardiac changes associated with anaerobic metabolism (for example, drop in ATP, and build-up of ATP catabolites and lactate). However, a recent experimental study in mice has demonstrated that RIPC is associated with cardiac ischaemic stress and accumulation of cardiac adenosine prior to index ischaemia [34]. This highlights the need to measure ischaemic-stress related metabolites in the hearts of patients undergoing surgery using RIPC.

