#### Markers in myocardial biopsies

The degree of ischaemic stress (anaerobic metabolism) associated with RIPC and cardioplegic arrest will be determined in ventricular biopsies. The metabolites that will be investigated in the ventricular biopsies are creatine phosphate, ATP, ADP, AMP, IMP, inosine, xanthine, hypoxanthine, adenosine, NAD^+^, lactate, alanine and glutamate. In addition, markers of potential signalling pathways that could be involved in RIPC will be monitored [23]. These secondary outcomes will be analysed in biopsies from the majority of participants, with a subgroup (about ten per group) being used for analyses of protein expression.

Expression of proteins implicated in RIPC protection in experimental studies will be determined by characterising the activation of intracellular kinases [35-37], the activation of the reperfusion injury salvage kinase (RISK) pathway, and the survivor activating factor enhancement (SAFE) pathway [38]. Gene expression for proteins that are activated will also be determined. Recent technological advances have provided new tools for screening and characterisation of activated proteins including mass spectrometry [39]. This is particularly important at the level of post-translational modifications of proteins (for example, phosphorylation), which are largely responsible for regulation of protein activity and function [40,41]. Therefore, the cardiac phosphoproteome will be measured in order to draw firm conclusions about the functional relevance of changes in proteins (proteome). A recent study has shown that RIPC cardioprotection in mice is linked with significant changes in several phosphoproteins associated with the z-disk area of the sarcomere [39]. Several of the phosphoproteins identified do not have antibodies available, thus making it difficult to measure using conventional methods. Therefore, we shall use these methods to screen for protein activation.

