#### Ventricular biopsies

Four ventricular biopsies will be collected from each participant. Biopsies will be collected in pairs, using a Tru-cut™ needle to obtain one biopsy from the apex of the left ventricle and one biopsy from the anterior wall of the right ventricle; the biopsies will be ‘snap’ frozen in liquid nitrogen and transferred to -80°C until processing. The first pair of biopsies will be collected after harvesting the mammary artery and before starting CPB. The second pair of biopsies will be collected 20 minutes after the end of ischaemic cardioplegic arrest.

Metabolites will be measured using HPLC or commercially available kits with the standard protocols established in our laboratories [43,44]. Western blotting will be used to determine the effect of RIPC and cardioplegic arrest on the activation of key proteins involved in the regulation of the MPTP (that is, ERK1/2, GSK3β, Akt). Signalling pathways linked to these enzymes will also be monitored. Appropriate antibodies will be used to detect phosphorylated or total amounts of the proteins [31,32,45]. In addition to protein expression, mRNA for all relevant proteins will be determined, and the results validated [45]. The cardiac proteome and phospho-proteome will be studied using isobaric tandem mass tagging and analysed by reverse phase nano-liquid chromatography/mass spectrometry.

The schedule of data collection is outlined in Table 1.

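### For biopsy markers, the RIPC effect before ischaemia is shown on its own only if a 10% group-by-time test is significant, so it may be diluted or not shown separately

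*Protocol article*

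**What the plan says.** All places are in the protocol article.

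- **Plan of analysis.** The biopsy markers come under the same modelling and reporting rule as troponin: "the secondary outcomes such as markers of kinase activity, oxidative stress and inflammation, are all measured multiple times in each patient". Kinase activity is measured only in the biopsies, so the rule reaches them.
- **Plan of analysis, stratum rule.** The group-by-stratum interaction is tested at 10%. If it is not significant, "otherwise, an overall treatment effect will be given".
- **Plan of analysis, time rule.** The next sentence carries the approach over: "Similarly, interactions of group and time and group and centre, will be explored", and "if statistically significant at the 10% level, the treatment effect will be reported for each time point separately".
- **Ventricular biopsies and Table 1.** There are two biopsy occasions. The first is just before bypass. For the second: "The second pair of biopsies will be collected 20 minutes after the end of ischaemic cardioplegic arrest". Under Trial interventions, RIPC is given before sternotomy, so both occasions follow it.
- **Possible mechanisms (Background).** The stated gap is that "little is known about the changes in the target tissue (myocardium) that are brought about by RIPC" before ischaemia and reperfusion. Most earlier work is said to have looked only afterwards.
- **Markers in myocardial biopsies.** Most participants contribute to the biopsy outcomes, "with a subgroup (about ten per group) being used for analyses of protein expression".

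Nothing exempts biopsy markers from the 10% rule or fixes the pre-bypass contrast as always reported.

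**The concern.** A rule that collapses effects over time unless they visibly differ can suit a series of similar post-operative blood samples. It suits the biopsies poorly. The first shows what RIPC does to myocardium that has not yet been arrested. The second shows the tissue after ischaemia and reperfusion. An average of the two answers neither question.

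Two things follow. If the interaction test is not significant, a change present mainly before ischaemia is reported as a diluted average. If the test is significant, the pre-bypass estimate has been selected partly for being large, so it tends to be too high. Which estimate readers see for each marker depends on the data. At stake is the mechanistic part of the trial, not the troponin result.

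**Working it through.** **Inputs from the protocol article.** Sample size: 60 per group overall and 30 per group in each stratum; cellular markers sized for 0.6 SD at 90% power (overall) and 0.72 SD at 80% power (within stratum), without repeated measures. Plan of analysis: interaction tested at 10%. Markers in myocardial biopsies: about ten per group for protein expression.

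**Assumptions.** Two-sided 5% for effects. Correlation ρ between the two biopsies of 0.3 to 0.5; the article gives these values for troponin and none for biopsies. 50 per arm stands for most participants. 20 per arm applies if ten per group means per stratum.

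**Step 1: the plan's own figures.** With SD 1, n per group = 2(z₀.₉₇₅ + z₀.₉₀)²/δ² = 2(1.960 + 1.282)²/0.6² = 58.4, so 59. At 60 per group, 0.6/√(2/60) = 3.286, and Φ(3.286 − 1.960) = 90.8%. For 0.72 SD at 30 per group, 0.72/√(2/30) = 2.789, and Φ(2.789 − 1.960) = 79.6%. Both reproduce, for a single ungated contrast at one biopsy.

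**Step 2: what the average shows.** The equally weighted average of the two effects is:
- 0.6 and 0 gives 0.30 (half)
- 0.6 and 0.3 gives 0.45 (three quarters)
- 0.6 and 0.6 gives 0.60 (no dilution)

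**Step 3: how often the 10% test is significant.** The SE of the difference between the two time-specific effects is √[(2/n) × 2(1 − ρ)].

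- Ten per arm, ρ = 0.3: SE = √(0.2 × 1.4) = 0.529; 0.6/0.529 = 1.134; probability = Φ(1.134 − 1.645) + Φ(−1.134 − 1.645) = 31%.
- 60 per arm, ρ = 0.5: SE = √(0.0333 × 1) = 0.183; 0.6/0.183 = 3.286; probability = 95%.

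| Per arm | Effect before bypass / after arrest (SD) | Formula, ρ 0.3 / 0.5 | Simulated (t tests, 20,000 trials) |
|---|---|---|---|
| 10 | 0.6 / 0 | 31% / 38% | about 28–37% |
| 20 | 0.6 / 0 | 48% / 60% | about 47–60% |
| 50 | 0.6 / 0 | 81% / 91% | about 81–91% |
| 60 | 0.6 / 0 | 87% / 95% | about 87–95% |
| 50 | 0.6 / 0.3 | 36% / 44% | about 35–44% |
| 60 | 0.6 / 0.3 | 40% / 50% | about 39–50% |

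Over a wider ρ of 0 to 0.7, the formula gives 25–53% at ten per arm and 75–99.5% at 60 per arm for 0.6 / 0, and 32–68% at 60 per arm for 0.6 / 0.3.

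**Step 4: the estimate when it is shown (0.6 / 0).** At ten per arm the pre-bypass estimate averages about 0.82–0.89 SD, roughly 35–49% too high. At 20 per arm the excess is about 16–26%, and at 50–60 per arm about 1–7%.

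**Step 5: pre-bypass effect both shown and significant at 5% (0.6 / 0), against always reporting it.**
- Ten per arm: 14–15% against about 25%
- 20 per arm: about 31–35% against about 45%
- 50 per arm: about 74–80% against about 84%
- 60 per arm: about 81–87% against about 90%

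**The case against.** A reader might infer that the pre-ischaemia effect will generally be halved or never reported. The documents do not support that.

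- **Size.** Most biopsy outcomes use most participants. At 50–60 per arm and the plan's own 0.6 SD, an effect confined to the first biopsy is usually shown separately and is barely inflated. Exact halving also needs no effect at all after arrest.
- **Wording.** The fallback to one overall effect is written for stratum and reaches time only through the linking word. The model contains the interaction, and geometric means are to be plotted, so the pre-bypass data need not vanish from the report.
- **Objective 3.** It names signalling mechanisms and no time point. The emphasis on the pre-ischaemia change comes from the background, and the biopsy section is also interested in cardioplegic arrest.
- **Averaging has a use.** If the effect persists fully (0.6 and 0.6), the average has about 93–98% power against about 84–91% for the single contrast at 50–60 per arm. Banning it would be a preference.
- **Small subset.** At ten per arm, even the direct contrast has only about 25% power. Sample size is the main limit there.
- **Baseline wording.** Sample size assumes no repeated measures for cellular markers, and the baseline-adjustment paragraph in Statistical analyses extends that adjustment to the proteome, using biopsies before and after arrest. On that reading there is one follow-up occasion and nothing to average.

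The first five points limit the claim and stand. The last does not rescue the plan. The first biopsy follows RIPC, so using it as a baseline would adjust for the pre-ischaemia effect instead of reporting it. Treating it as an outcome brings the 10% rule back. Nor does any of this guarantee the pre-bypass contrast.

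**Conclusion.** The point holds in a limited form. As written, separate reporting of the RIPC effect before ischaemia depends on a 10% interaction test; otherwise a pre/post-arrest average may stand in for it.

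The problem is clearest in two settings. One is the protein-expression subset, where a pre-bypass-only effect of 0.6 SD is shown separately in about 28–37% of trials at ten per arm, or 47–60% if the subset is 20 per arm, and is overestimated when shown. The other is an effect that half persists after arrest, shown separately in only about 35–50% of trials even at 50–60 per arm, with the average near 0.45 SD. For a large pre-bypass-only effect in most participants, the practical loss is small.

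These figures rest on an assumed biopsy correlation, an assumed effect pattern, and reading the overall-effect fallback as applying to time. The outcomes are secondary but carry the trial's mechanistic aim, so the change should be made; it does not threaten the primary result.

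**What to change.** Add to Plan of analysis, for example:

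> For biopsy markers, the RIPC-minus-sham difference with its 95% confidence interval will always be reported at the pre-CPB biopsy and at the biopsy 20 minutes after the end of arrest, whatever the group-by-time P value. The pre-CPB biopsy is a post-intervention outcome and will not be used as a baseline covariate when estimating the effect of RIPC. A time-averaged effect may be given in addition.

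Reconcile the baseline-adjustment paragraph with this, and state whether ten per group in the protein-expression subset is per arm overall or per arm within each stratum.

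The cost is two estimates per marker instead of one. No new data or samples are needed. The change does not cure the low power of the small subset; it removes the data-dependent choice of which estimate is shown.

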### Trial interventions

#### Remote ischaemic preconditioning (intervention)

A research nurse will apply the cuff for administering RIPC under the operating cover, placing the cuff around the participant’s upper arm, after induction of anaesthesia and before sternotomy, CPB and cardioplegic arrest. RIPC will be induced as described by others [8,10]. It will comprise four 5 minute cycles of upper limb ischaemia, induced by a blood pressure cuff inflated to 200 mmHg, with an intervening 5 minutes of reperfusion by deflating the cuff. For participants with systolic blood pressure >185 mmHg, the cuff will be inflated at least 15 mmHg above the participant’s systolic blood pressure.

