It is important to emphasise that analyses of all outcomes will adjust for baseline levels of outcomes. Therefore, although there will be heterogeneity between patients within groups, the analyses will take this heterogeneity into account by quantifying the effects of the design factors after removing variation attributable to individual participants. This approach extends to the analyses of the proteome/phosphoproteome since data will be available for biopsies from the same ventricle of the same participant before and after cardioplegic ischaemic arrest. In effect, this allows us to focus on detecting changes in the same tissue (left or right ventricle) in two different pathologies.

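### Baseline adjustment is extended to biopsy outcomes although every biopsy is taken after RIPC or sham, in conflict with the plan's own definition of baseline

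*Protocol article*

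**What the plan says.** **Timing of the intervention.** The section on the RIPC intervention places the cuff cycles "after induction of anaesthesia and before sternotomy, CPB and cardioplegic arrest". Under Challenges in study procedures, a run that is incomplete in the anaesthetic room is still finished before the chest is opened: "the intervention is completed in theatre as the patient is being prepared for surgery before sternotomy".

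**Timing of the biopsies.** The Ventricular biopsies section gives four biopsies in two left/right pairs: "The first pair of biopsies will be collected after harvesting the mammary artery and before starting CPB", and "The second pair of biopsies will be collected 20 minutes after the end of ischaemic cardioplegic arrest". Table 1 puts the first pair immediately before CPB, below the blood sample taken straight after RIPC.

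**Analysis.** The Plan of analysis makes two statements:

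- In describing the mixed model, it names kinase activity among the markers measured repeatedly, includes intervention by time, and says: "Baseline (pre-intervention) measures, where available, will be analysed jointly with the post-intervention measure(s".
- In its closing paragraph it says: "It is important to emphasise that analyses of all outcomes will adjust for baseline levels of outcomes". It carries this approach over to the proteome and phosphoproteome "since data will be available for biopsies from the same ventricle of the same participant before and after cardioplegic ischaemic arrest", with the aim of detecting changes within the same tissue.

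**The concern.** No biopsy precedes the intervention. If the closing paragraph is applied to biopsies, the only candidate for baseline is the pre-CPB pair, which was taken after RIPC or sham. Conditioning on it, or subtracting it, removes from the post-arrest comparison whatever part of the RIPC effect was already present before bypass.

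The third objective is to investigate signalling mechanisms, and the Background presumes that the limb signal triggers changes in the myocardium that lead to protection. It also says of the period before ischaemia and reperfusion: "Similarly, little is known about the changes in the target tissue (myocardium) that are brought about by RIPC". The pre-CPB biopsy is the sample that can address that gap. Used as a baseline, it would no longer be read as a result, and a mechanistic null could come from the choice of analysis.

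**Working it through.** **1. Order of events**

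| Step | Source |
|---|---|
| Blood sample before RIPC | Blood samples; Table 1 |
| RIPC or sham, completed before sternotomy | RIPC intervention; Challenges in study procedures |
| Blood sample after RIPC | Blood samples; Table 1 |
| First biopsy pair, before CPB | Ventricular biopsies; Table 1 |
| Second biopsy pair, 20 minutes after arrest | Ventricular biopsies; Table 1 |

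Blood markers have a pre-intervention value. Biopsy markers have none.

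**2. The plan's own figures for cellular markers**

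The Sample size section gives 0.6 SD at 90% power with 60 per group, and 0.72 SD at 80% power within a stratum (30 per group). No alpha is stated for these figures; two-sided 0.05 is assumed, in line with the 95% confidence intervals. For an unadjusted two-group comparison, the minimum detectable difference is (z for alpha + z for power) × √(2/n):

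- 3.2415 × √(2/60) = 0.592
- 2.8016 × √(2/30) = 0.723

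The normal approximation gives power of 0.908 at 0.6 SD and 0.796 at 0.72 SD. The stated figures therefore reproduce with no gain from any covariate.

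**3. What adjustment for the pre-CPB biopsy estimates**

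Let d1 and d2 be the RIPC effects, in SD units, at the pre-CPB and post-arrest biopsies, and r their within-group correlation.

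- Covariate adjustment estimates d2 − r·d1.
- A change score estimates d2 − d1.
- A joint model that forces the group means to be equal at the pre-CPB biopsy has the same problem as covariate adjustment.

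The documents give no r for biopsy markers. Troponin I has a pre-post correlation of 0.3; 0.3 to 0.7 is assumed here. The values of d1 and d2 are also assumed. The plan's 0.6 SD is a detectable difference for cellular markers in general, not a stated effect at either biopsy.

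| d1 | d2 | Adjusted, r = 0.3 | r = 0.5 | r = 0.7 | Change |
|---|---|---|---|---|---|
| 0 | 0.6 | 0.60 | 0.60 | 0.60 | 0.60 |
| 0.3 | 0.6 | 0.51 | 0.45 | 0.39 | 0.30 |
| 0.6 | 0.6 | 0.42 | 0.30 | 0.18 | 0 |

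For example, 0.6 − 0.5 × 0.6 = 0.30.

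**4. Consequence for power with 60 per group**

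The standard error of the adjusted effect is √[(1 − r²) × (2/60) × (1 + d1²/4)]. The last factor allows for the group difference in the covariate.

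- d1 = d2 = 0.6: the factor is 1.09. At r = 0.5 the standard error is √(0.75 × 0.0333 × 1.09) = 0.165, so 0.30/0.165 = 1.82 and power is 44%. A simulation of 4,000 trials gave an estimate of 0.299 and power of 43%, against 0.599 and 90.5% unadjusted. At r = 0.3 and 0.7 the formula gives 64% and 26%. For a change score, rejection falls to the 5% alpha level.
- d1 = 0.3, d2 = 0.6: the factor is 1.0225, and adjusted power is between 80% and 84%, against 91% unadjusted.
- d1 = 0: there is no bias, and covariate adjustment would raise power to 93% or more.

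These powers assume 60 per group. Protein expression is planned in a subgroup of about ten per group, where power is far lower on any analysis. The bias does not depend on sample size.

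**The case against.** Nowhere does the plan call the pre-CPB biopsy a baseline or list it as a covariate. The model description limits baseline to pre-intervention measures where these exist, which excludes biopsies. It also places kinase activity, which the documents measure only in biopsies, in a mixed model with intervention by time, where both biopsies are outcomes and the effect is kept. The closing paragraph's stated aim of removing variation between participants could describe a participant random effect. Change across arrest is a fair question in its own right, and the sample size shows no reliance on a biopsy covariate. For energy metabolites, the Background does not expect RIPC to produce anaerobic changes, although it cites one contrary mouse study.

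Most of this stands. A reader might infer that the plan is certain to attenuate, cancel or even reverse the RIPC effect on the biopsy markers. The documents do not support that: the model description permits an analysis without the bias, and any loss requires an early shift whose size the documents do not give. Nor is the pre-CPB difference simply discarded, since effects are reported by time point if the interaction is significant at the 10% level.

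What does not fall away is the conflict. The closing paragraph states its rule with emphasis and for all outcomes, and it names the proteome on the strength of a biopsy taken after the intervention. Two readings that give different estimates are open. Under the 10% rule, moreover, an RIPC effect of similar size at both biopsies would not trigger reporting at each.

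**Conclusion.** The point holds as an internal conflict with a conditional bias. The closing paragraph extends baseline adjustment to biopsies that have no pre-intervention value, against the definition of baseline given earlier in the same section. If it is followed, and if RIPC has shifted the marker before CPB as the Background presumes for signalling, part of the post-arrest effect is lost: 30%, 50% or 70% for equal effects at r of 0.3, 0.5 or 0.7, and all of it for a change score. The early effect, its persistence and the correlations are assumptions; with no early effect there is no bias.

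The explicit extension concerns the proteome and phosphoproteome. Other biopsy markers are reached only through the reference to all outcomes. The primary outcome is not affected. This should be fixed, as a matter for the secondary mechanistic outcomes.

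**What to change.** Amend the closing paragraph of the Plan of analysis as follows:

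- Baseline adjustment applies only to markers with a sample taken before RIPC or sham.
- For all biopsy markers, the pre-CPB and post-arrest biopsies are both outcomes in the mixed model already described, adjusted for surgical stratum and centre. Group-by-time means are not constrained to be equal at the pre-CPB biopsy.
- RIPC minus sham is reported at each biopsy with a 95% confidence interval, whatever the result of the interaction test.
- Change across arrest may be reported as a separate, labelled question, not as the baseline-adjusted RIPC effect.

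The cost is wording in the protocol and analysis plan, with no new data. Any precision gained by using the first biopsy as a covariate is given up, which matters for markers that RIPC does not shift early. The stated 0.6 and 0.72 SD for cellular markers already correspond to an unadjusted comparison, so no planned power is lost.
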